## 1.2 Investigational Drug Background

Drug name: rAAV2/8-hCYP4V2 Ophthalmic Injection, developed by Chigenovo Co., Ltd. and provided by OBiO Technology (Shanghai) Corp., Ltd. The internal code is ZVS101e in Chigenovo Co., Ltd., and C035 Injection in OBiO Technology (Shanghai) Corp., Ltd.

rAAV2/8-hCYP4V2 Ophthalmic Injection is a recombinant adeno-associated virus type 8 vector expressing human CYP4V2 protein. The genome includes the ITR of rAAV2 adeno-associated virus and human CYP4V2 gene expression frame, and is 3 kb in length. rAAV2/8-hCYP4V2 vector has a specific tropism for retinal cells, expresses human CYP4V2 protein and normally exerts physiological functions.

rAAV2/8-hCYP4V2 Ophthalmic Injection is prepared by transfection of multiple plasmids into suspended human embryonic kidney cells, large-scale fermentation, and high purification. It contains suitable stabilizers, and no preservatives and antibiotics. Clinical samples are manufactured under current Good Manufacturing Practice (GMP) conditions. The specification is based on the Technical Guidelines for Human Gene Therapy Studies and Drug Product Quality Control and Chinese Pharmacopoeia 2015, and is set with reference to the marketed gene therapy drug Luxturna or other rAAV vectors. Sample testing met specification.

After subretinal injection of rAAV2/8-hCYP4V2 Ophthalmic Injection in patients with BCD, recombinant adeno-associated virus rAAV2/8-hCYP4V2 can efficiently infect retinal cells and express CYP4V2 protein in photoreceptor cells, and the expressed CYP4V2 protein can compensate for the function of the deleted protein, thus playing a huge therapeutic role in the functional recovery of retina.

At present, preclinical studies, including in vitro pharmacodynamics, in vivo pharmacodynamics, pharmacokinetics and toxicology, have been completed for rAAV2/8-hCYP4V2 adeno-associated virus Ophthalmic Injection, and the efficacy and safety of rAAV2/8-hCYP4V2 gene replacement therapy have been preliminarily demonstrated, as detailed in the Investigator's Brochure.

Based on these preclinical study results and clinical practical needs, we intend to enroll patients with BCD to evaluate the safety and preliminary efficacy of rAAV2/8-hCYP4V2 gene replacement therapy and preliminarily explore the large-scale application of rAAV2/8-hCYP4V2 gene replacement therapy technology.

# 2. Study Objectives

**Primary Objective:** To evaluate the safety of a single subretinal injection of rAAV2/8-hCYP4V2 in patients with Bietti's crystalline dystrophy (BCD).

**Secondary Objective:** To preliminarily explore the clinical efficacy of rAAV2/8-hCYP4V2 gene replacement therapy.

# 3. Study Design

## 3.1 Overall Design

This is a single-center, open-label, single-arm and single-dose study and aimed to evaluate the safety and preliminary efficacy of the investigational drug in patient with BCD.

**Selection Criteria for Target Eye**

The target eye must meet the following requirements:

1) BCVA is counting finger to 0.3 (equivalent to Snellen visual counting finger to 20/63); able to perform visual examination and retinal function test; macular photoreceptor layer, that is, the outer nuclear layer can be observed in macular area under standard optical coherence tomography (OCT);

2) The eye with poorer visual acuity in both eyes of the candidate subject is the target eye. Note: For all subjects, only one eye is designated as the "target eye" (i.e., treated eye). If both eyes of patients meet the inclusion criteria, the target eye will be medically determined by the investigator.

**Safety Study**

The investigational product rAAV2/8-hCYP4V2 Ophthalmic Injection is a gene replacement therapy product. In preliminary safety clinical study (ClinicalTrials No.: NCT04722107), enrollment, administration, and 3-month safety and efficacy observation have been completed for 3 subjects. During the observation period, no drug- or treatment-related serious adverse reactions occurred in any of the 3 subjects; meanwhile, 2 of the subjects showed significant improvements in visual acuity and MLMT score. It can be seen that the clinical dose of 5×10^8^ vg/uL has good safety and reflects certain efficacy. In this clinical study, additional 9 subjects are planned to be enrolled, and a total of 1 dose group, 7.5×10^10^ vg, is set. After one subject is enrolled first and no significant toxic and side effects are observed within 14 days after administration, the study in the second subject may be initiated. After the second subject completes administration and no significant toxic and side effects are observed within 14 days, the study in the third subject may be initiated; and so on. While conducting safety study, tear and blood samples are collected from subjects to detect DNA of rAAV2/8 virus and immune responses against the therapeutic vector.

**Preliminary Exploratory Study of Efficacy**

Clinical efficacy is preliminarily assessed by BCVA (ETDRS chart), macular microperimetry, mfERG, color vision, dark-adapted contrast sensitivity, and MLMT.

## 3.2 Rationale for Dose Setting

The investigational drug rAAV2/8-hCYP4V2 Ophthalmic Injection is a gene replacement therapy. In preliminary safety clinical study (ClinicalTrials No.: NCT04722107), enrollment, administration, and 3-month safety and efficacy observation have been completed for 3 subjects. During the observation period, no drug- or treatment-related serious adverse reactions occurred in any of the 3 subjects; meanwhile, 2 of the subjects showed significant improvements in visual acuity and MLMT score. It can be seen that the clinical dose of 5×10^8^ vg/uL has good safety and reflects certain efficacy.

Preclinical pharmacodynamic experiment has preliminarily demonstrated that 1 uL of the following concentrations of rAAV2/8-hCYP4V2 were injected into the subretinal space of CYP4V2 knockout mice: CYP4V2 protein was expressed in 1×10^8^, 5×10^8^, 1×10^9^, 3×10^9^, 6×10^9^ and 1×10^10^ (unit: vg/uL), and the 6-month in vivo observation at following three doses of 3×10^9^ vg, 6×10^9^ vg and 1×10^10^ vg showed that 3×10^9^ vg had a significant therapeutic effect without obvious toxicities, and 6×10^9^ vg and 1×10^10^ vg had evident efficacy in the early stage, but obvious retinal toxicity in the later stage.

Referring to Luxturna (produced by Spark, intended for LCA patients carrying RPE65 gene mutation), the only gene replacement therapy marketed in the field of inherited retinal degeneration, the dose escalation concentration of Luxturna is designed as: 1×10^8^ (150 uL), 3.2×10^8^ (150 uL) and 5×10^8^ (300 uL) (unit: vg/uL). The dose escalation study results showed that all of the above three concentrations had therapeutic effect without obvious toxicities. The recommended Phase 3 concentration of Luxturna was 5×10^8^ vg/uL (300 uL), which was the maximum concentration tested in vivo.

Referring to the clinical study data of RPGR gene replacement therapy drug published in Nature Medicine in February 2020, the dose escalation concentrations were designed as six doses: 5×10^7^ (40-100 uL), 1×10^8^ (40-100 uL), 5×10^8^ (30-100 uL), 1×10^9^ (60-100 uL), 2.5×10^9^ (50-150 uL) and 5×10^9^ (30-80 uL) (unit: vg/uL). The results showed that 5×10^7^ vg/uL and 1×10^8^ vg/uL groups had no significant improvement, 5×10^8^ vg/uL group had significant increase, and 7 of 9 subjects in the three high concentration groups showed mild inflammatory reaction, which could be effectively managed after hormone therapy.

Based on the preclinical results of the investigational drug and comparison with similar drugs, and referring to the dose design for Phase 1 dose escalation and recommended clinical dose of the similar marketed drug Luxturna, the concentration gradient selected in this project is: 1×10^8^ vg/uL, 5×10^8^ vg/uL, 1×10^9^ vg/uL and 3×10^9^ vg/uL, and the injection dose is 150 uL. The concentration selected for this preliminary experiment is 5×10^8^ vg/uL, 150 uL, that is, each subject is injected with a total of 7.5×10^10^ vg of investigational drug.

## 3.3 Definition of End of Study

The study ends when the last subject completes follow-up and the investigator completes all assessments and visit records.

**Required by Investigator**

The investigator may not be able to continue the study for some reasons. The investigator must inform the subject, sponsor, Ethics Committee and clarify the reason for terminating a clinical study.

**Required by Sponsor**

Reasons for sponsor's requirement for early termination of the study or early termination of the study in one study site:

1) Funding reasons;

2) Administrative reasons;

3) The investigator cannot follow the protocol;

4) The investigator cannot recruit enough subjects;

5) Safety considerations.

The sponsor must inform the investigator, Ethics Committee in writing and clarify the reasons before terminating a clinical study.

# 4. Study Population

## 4.1 Inclusion Criteria

Subjects who meet all of the following inclusion criteria are considered eligible for participation in this study.

1) Age ≥ 18 years (inclusive) at the time of informed consent;

2) Patients with clinically confirmed Bietti's crystalline dystrophy (BCD);

3) Carrying two causative mutations in CYP4V2 gene confirmed by genetic testing;

4) Meet selection criteria for target eye;

5) The subject and his/her spouse agree to take effective contraceptive measures during the study and within 1 year after administration;

6) Voluntarily participate in this clinical study and have signed informed consent form.

## 4.2 Exclusion Criteria

Subjects meeting any of the following criteria will not be eligible to participate in this study.

1) The patient lacks sufficient viable retinal photoreceptor cells, has less than 1 disc area of retina photoreceptor cells or has a retinal thickness of less than 100 μm.

2) Active choroidal neovascularisation (CNV) lesion secondary to BCD in the target eye judged by the investigator; or other ocular disorders that would preclude surgery or interfere with interpretation of the study endpoints;

3) Medications within 3 months prior to screening that may affect study observation (e.g., Lucentis, Avastin, aflibercept, conbercept, triamcinolone acetonide, steroids, etc);

4) The target eye has received the following intraocular surgical treatments (PDT, vitrectomy, cataract surgery and retinal laser therapy required during the clinical study, periocular vascular bypass surgery, etc.);

5) Currently taking or may require systemic medications that can cause ocular toxicity, such as Psoralen, Risedronate, or Tamoxifen;

6) Hypersensitivity to any component of the investigational drug, or allergic constitution (e.g., allergy to two or more drugs or food);

7) Abnormal findings of physical examination, vital signs, laboratory tests (hematology, urinalysis, blood biochemistry, coagulation function, immunological examination, female blood pregnancy test), 12-lead ECG, chest X-ray judged by the investigator as clinically significant;

8) Having any past or present medical history that may affect the safety of the study or the metabolic process of the drug, especially the medical history of cardiovascular, hepatic, renal, endocrine, gastrointestinal, pulmonary, neurological, hematological, oncologic, immunological or metabolic disorders and others that are thought clinically significant by the investigator;

9) Participation in any clinical study of drug or medical device within 3 months prior to screening;

10) Patients with rAAV neutralizing antibody titer greater than 1:1000 detected by immunogenicity test;

11) Females who are pregnant or lactating;

12) Subjects who are not suitable for participation in this clinical study due to other reasons judged by the investigator.

## 4.3 Withdrawal Criteria

1) Subject is unwilling or unable to continue to participate in the study (withdrawal of informed consent, non-adverse event reasons);

2) Subject loss to follow-up;

3) Serious non-compliance with study requirements;

4) The subject presents any adverse event (clinical adverse event, laboratory test abnormality) that precludes continuation of the clinical study, diseases or other conditions found during the study;

5) The investigator judges that the subject should withdraw from the study;

6) Other reasons.

The date and reason for subject withdrawal will be recorded on the Case Report Form (CRF). Withdrawer due to adverse events should be followed up until recovery or stabilization.

# 5. Study Intervention

## 5.1 Investigational Drug

### 5.1.1 Investigational drug information

**Name:** rAAV2/8-hCYP4V2 Ophthalmic Injection (the internal code is ZVS101e in Chigenovo Co., Ltd., and C035 Injection in OBiO Technology (Shanghai) Corp., Ltd.)

**Strength:** 1.0×10^12^ vg/mL, 0.3 mL/vial.

**Route of Administration:** Subretinal injection.

**Storage Conditions:** Long-term storage at ≤ -70°C, short-term storage at 2-8°C. Stored in the original carton in the dark until use.

**R&D Unit/Supplier:** Chigenovo Co., Ltd.

**Manufacturer:** OBiO Technology (Shanghai) Corp., Ltd.

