# Protocol Synopsis

| **Sponsor:** Beijing Tongren Hospital, Capital Medical University |
| --- |
| **Cooperative Unit:** Chigenovo Co., Ltd. |
| **Study Phase:** Investigator-initiated trial |
| **Study Title:** A Safety Study of a Single Subretinal Injection of rAAV2/8-hCYP4V2 Gene Replacement Therapy in Patients with Bietti's Crystalline Dystrophy (BCD) |
| **Indication: Bietti's crystalline dystrophy (BCD)** |
| **Study Objectives:**  Primary objective: To evaluate the safety of a single subretinal injection of rAAV2/8-hCYP4V2 in patients with Bietti's crystalline dystrophy (BCD).  Secondary objective: To preliminarily explore the clinical efficacy of rAAV2/8-hCYP4V2 gene replacement therapy. |
| **Investigational Drug:** rAAV2/8-hCYP4V2 Ophthalmic Injection, provided by Chigenovo Co., Ltd. and manufactured by OBiO Technology (Shanghai) Corp., Ltd. (The internal code is ZVS101e in Chigenovo Co., Ltd., and C035 Injection in OBiO Technology (Shanghai) Corp., Ltd.)  **Strength:** 2×10^12^ vg/mL, 0.2 mL/vial, diluted to 5×10^8^ vg/uL before use  **Injection Volume:** 150 uL  **Dose of Administration:** 7.5×10^10^ vg  **Method of administration:** Subretinal injection |

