| **Sample Size:** 3 + 9 expected |
| **Study Procedure:**  Eligible subjects will be administered prednisone 3 days (Day -3) prior to dosing for 10 days at a dose of 1 mg/kg/day for the first 3 days. On the day of ZVS101e administration, vitrectomy is performed on the target eye according to the clinical practice, and 150 uL of the ZVS101e is injected into the subretinal space through a sterile injection needle for single use in strict accordance with the package insert of the drug. After surgery, routine treatment after vitrectomy is performed and prednisone is orally administered at 0.5 mg/kg/day for an additional 7 days without any treatment in the fellow eye. Patients have to lie supine for at least 14 hours following treatment (according to the clinical study results of Luxturna, 150 uL of the treatment vector was completely absorbed approximately 14 hours after local injection).  On D1, D2, D3, D7, D14, D28, D60, D90, D180, D270 and D365 after injection and at 15 months after the end of observation period, safety assessments were performed at corresponding time points, adverse events and concomitant medications are recorded for safety evaluation.  According to the blood collection points, biological samples are collected for relevant safety and immunogenicity evaluation.  Ocular functional tests (BCVA- ETDRS chart, macular microperimetry, mfERG, dark-adapted contrast sensitivity, and MLMT) and morphological test (color fundus photography, fundus autofluorescence (FAF) and OCT) are performed at visit points during the study to preliminarily evaluate the efficacy of the vector. |

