### 5.1.2 Dosing regimen

In this clinical study, additional 9 subjects are planned to be enrolled, and a total of 1 dose group, 7.5×10^10^ vg, is set. After one subject is enrolled first and no significant toxic and side effects are observed within 14 days after administration, the study in the second subject may be initiated. After the second subject completes administration and no significant toxic and side effects are observed within 14 days, the study in the third subject may be initiated; and so on. While conducting safety study, lacrimal fluid and blood samples are collected from subjects to detect DNA of rAAV2/8 virus and immune responses against the therapeutic vector.

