### 5.1.3 Packaging and labeling

Packaging: The investigational drug is packaged by the cooperative unit.

Labeling: The label should be indicated with product name, batch number, strength, shelf life, storage condition, entrusting party, manufacturer, "For clinical study use only", etc.

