# 9. Statistical Considerations

## 9.1 Statistical Hypothesis and Sample Size Estimation

### 9.1.1 Statistical hypothesis

This study is an exploratory study on the trend of safety and efficacy, without statistical hypothesis.

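### The synopsis and section 5.1.1 give vial strengths that differ two-fold for the same product, and the protocol never states the dilution that goes with either

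*Protocol*

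**What the plan says.** The synopsis, under Investigational Drug, gives the strength as "2×10^12^ vg/mL, 0.2 mL/vial, diluted to 5×10^8^ vg/uL before use". Section 5.1.1 gives it as "1.0×10^12^ vg/mL, 0.3 mL/vial", with no dilution step. Both entries carry the same product name, the same two internal codes and the same manufacturer.

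The intended dose is stated consistently. Section 3.2 says "The concentration selected for this preliminary experiment is 5×10^8^ vg/uL, 150 uL" and that "each subject is injected with a total of 7.5×10^10^ vg of investigational drug". Section 5.1.2 adds that "a total of 1 dose group, 7.5×10^10^ vg, is set".

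On preparation, the Study Procedure part of the synopsis has the injection carried out "in strict accordance with the package insert of the drug" and gives no dilution factor. Section 5.1.3 lists strength among the required label items: "The label should be indicated with product name, batch number, strength".

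**The concern.** One product cannot have both strengths unless there are two presentations, and the protocol mentions none. It does not describe a second batch or a change between the 3 subjects already treated and the 9 to be added. Concentration and fill volume both differ, so these read as two complete and incompatible vial descriptions, not as one mistyped digit.

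Section 5 is where a reader would look for preparation details, and it gives none: 5.1.1 has a strength without a dilution, 5.1.2 has only the total vg, and 5.1.3 and 5.1.4 deal with labelling, storage and accountability. The only mention of dilution sits in the synopsis, attached to the other strength.

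The treatment is a single subretinal injection, so a preparation error cannot be corrected afterwards. With one dose group, the safety summaries in section 9.3.3 all refer to one dose level. An unnoticed mismatch would pool unequal actual doses under that label.

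**Working it through.** **Inputs**

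- Target concentration 5×10^8 vg/uL, volume 150 uL, total 7.5×10^10 vg (synopsis; section 3.2).
- Synopsis vial: 2×10^12 vg/mL, 0.2 mL.
- Section 5.1.1 vial: 1.0×10^12 vg/mL, 0.3 mL.

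**1. The plan's own dose.** Dose = concentration × volume = 5×10^8 × 150 = 7.5×10^10 vg. This reproduces exactly.

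**2. What each vial implies.** Stock in vg/uL = strength per mL ÷ 1000. Dilution factor = stock ÷ 5×10^8. Stock needed for 150 uL = 150 ÷ dilution factor. Vial content = strength × fill volume.

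| | Synopsis vial | Section 5.1.1 vial |
|---|---|---|
| Stock | 2×10^9 vg/uL | 1×10^9 vg/uL |
| Dilution factor | 2×10^9 ÷ 5×10^8 = 4 | 1×10^9 ÷ 5×10^8 = 2 |
| Stock per 150 uL | 150 ÷ 4 = 37.5 uL | 150 ÷ 2 = 75 uL |
| Vial content | 2×10^12 × 0.2 = 4×10^11 vg | 1×10^12 × 0.3 = 3×10^11 vg |

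The larger fill volume does not offset the lower strength: the two vials differ in total content as well.

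**3. Strength and dilution crossed.** Delivered dose = (actual stock ÷ dilution used) × 150.

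| Actual vial | Dilution used | Concentration | Dose in 150 uL | Ratio to plan |
|---|---|---|---|---|
| 2×10^12 vg/mL | 4-fold | 5×10^8 vg/uL | 7.5×10^10 vg | 1.0 |
| 2×10^12 vg/mL | 2-fold | 1×10^9 vg/uL | 1.5×10^11 vg | 2.0 |
| 1×10^12 vg/mL | 2-fold | 5×10^8 vg/uL | 7.5×10^10 vg | 1.0 |
| 1×10^12 vg/mL | 4-fold | 2.5×10^8 vg/uL | 3.75×10^10 vg | 0.5 |

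A reader who used section 5.1.1 alone and did not dilute would draw up 1×10^9 × 150 = 1.5×10^11 vg, again twice the plan.

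**4. Would the fill volume expose a mistake?** No. The crossed preparations need 75 uL from a 200 uL vial or 37.5 uL from a 300 uL vial. Both are available, so neither vial would run short.

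**5. The size of the error on the protocol's own scale.** Section 3.2 lists a project gradient of 1×10^8, 5×10^8, 1×10^9 and 3×10^9 vg/uL. A two-fold excess lands on the next step above the one chosen. In the RPGR study that section 3.2 cites, the three highest concentrations begin at 1×10^9 vg/uL, and 7 of 9 subjects in those groups had inflammation, described as mild and manageable. Half the concentration, 2.5×10^8, falls between the level reported there without significant improvement (1×10^8) and the level reported with it (5×10^8).

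**The case against.** The best counter-argument is that only the description of the stock is in conflict. Concentration, volume and total dose agree wherever they appear, and no calculation in the protocol is wrong. Neither passage prescribes a dilution factor; the 4-fold and 2-fold figures are derived here. The synopsis fixes the end concentration, which gives the planned dose from either vial if the strength of the vial in hand is used. The label must show strength and batch number, and the package insert governs the procedure. Section 5.1.1 is a product-information list, where a preparation step need not appear.

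Most of this stands, and it limits the claim. The point is an internal inconsistency, not a miscalculated dose. A wrong dose requires someone to rely on the protocol's strength instead of the label, or to skip the dilution. The four-fold case, injecting the synopsis vial undiluted, can be set aside because the synopsis line itself calls for dilution.

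The contradiction remains. The package insert is not among the documents, so whether it settles the preparation is unknown. The safeguards lower the likelihood of an error; they do not tell a reader which vial description the protocol means. Logging drug use (section 5.1.4) and recording any overdose (section 5.2.3) help only once a discrepancy has been noticed.

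**Conclusion.** The concern holds. The synopsis and section 5.1.1 contradict each other on strength (two-fold) and on fill volume (0.2 against 0.3 mL), and no text reconciles them. If the dilution for one vial is applied to the other, the delivered dose is 1.5×10^11 or 3.75×10^10 vg against a planned 7.5×10^10 vg, a factor of two in either direction.

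Those figures assume that the full 150 uL is injected and that the vial really has one of the two stated strengths. How likely such a mix-up is cannot be judged from the protocol. Which strength is correct cannot be settled from it either, and this review takes no position on that. The correction should be made before further subjects are dosed, because the administration is single and irreversible and the trial reports on one dose level only.

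**What to change.** Reconcile the strength and fill volume in the synopsis and section 5.1.1 against the batch release documents, so that both carry the same description. State the matching dilution step beside the strength in both places, and check that it agrees with the package insert.

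If more than one presentation has been used, for instance between the first 3 and the additional 9 subjects, say so and identify who received which. Record vial strength, dilution applied and calculated vg for each subject, so that the single dose level in the safety and efficacy summaries can be verified.

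The cost is a protocol correction and a short addition to the dispensing log. The target dose, design, visits and sample size are untouched.
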